#### Self-Rated Health

Self-rated health will be assessed using the EQ-5D visual analogue scale [41], where participants rate their overall health on a scale from 0 (“worst imaginable health”) to 100 (“best imaginable health”).

#### Additional Individual Components of Diet and Physical Activity Outcomes

In addition to the composite diet quality score (primary outcome), we will examine the effectiveness of the PRIMI app on the 4 key diet indicators individually as secondary outcomes (ie, intake of vegetables, fruits and berries, sweet beverages, and sweet and savory snacks). Furthermore, beyond analyzing the effects on moderate-to-vigorous physical activity (primary outcome), we will also assess vigorous and moderate physical activity separately as secondary outcomes. All behavioral measures are presented in Multimedia Appendix 2.

#### Process Evaluation

User experience data will be collected at the 6-month follow-up by asking intervention group participants about their experiences of the PRIMI app. We will also conduct a process evaluation based on qualitative data collected through interviews with a subsample of women to obtain richer data and a deeper understanding of how the mHealth intervention was perceived and appreciated by the women [42-45].

Furthermore, automatically collected use data will be used to investigate how the app was used by participants, including the number of sessions, the number of registrations, and the time spent on the app.

#### Demographic Variables

Women will report demographic and descriptive variables such as age, educational attainment, birth country, parity, time since childbirth, and adverse pregnancy outcomes during their last pregnancy.

### Statistical Analysis and Power Considerations

Intervention effects will be analyzed according to the intention-to-treat principle using mixed linear regression models (with a random level for the individual) examining the effect of the group allocation (intervention vs control) on the primary and secondary outcomes. Data analyses will be conducted with available data as well as with missing data imputed using multiple imputations [46]. The primary analysis is the intervention effect on diet quality and moderate-to-vigorous physical activity at the 6-month follow-up adjusted for baseline values as we have done previously [20,21,25] as this procedure has the advantage of being robust to imbalances at baseline and regression toward the mean [47]. Furthermore, all models will be adjusted for age and time since childbirth. We will also consider adjusting for educational attainment and birth region provided that the sample size and distribution of these variables allow for meaningful adjustment (ie, empirical positivity).

We will also conduct a secondary per-protocol analysis including women who have used the PRIMI app (ie, engaged in at least one session) during at least 5 of the 26 intervention weeks. We will also examine whether certain variables moderate (eg, age, parity, educational attainment, birth region, self-efficacy, and health literacy) or mediate (eg, self-efficacy and health literacy) the effect of the PRIMI app on the outcomes.

A total of 100 women (50 per group) will provide at least 80% power (α=.05) to detect a minimally clinically relevant effect size of a 0.35-SD difference in the primary and secondary outcomes; we simulated trials with different sample sizes and parameter variance (*k*=100 simulations per specification) to find a suitable level whereby there was at least 80% power to detect the relevant effect [48]. It may be argued that smaller effect sizes than this may have limited clinical value, and thus, we consider the sample size sufficient. We aim to recruit 200 women (100 per group) to account for a potential dropout rate of up to 50%. However, we may consider recruiting fewer participants if the actual dropout rate is lower. To prevent dropout, participants will receive a mobile phone SMS text message reminding them about the 6-month follow-up questionnaire a few days before the questionnaire link is sent. Participants who have not completed the questionnaire within a few days will be contacted via phone to be assisted in completing it.

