**Methods:**

A 2-arm randomized controlled trial will be conducted to examine the effectiveness of the PRIMI app. First-generation migrant women who have given birth within 6 months, are aged 18 years or older, and prefer to receive health-related information in any of the provided languages are eligible to participate in the study and will be recruited through health care services in Sweden. The women will be randomized to the control group (standard care, eg, parental guidance and support within child health care) or the intervention group (PRIMI app+standard care) in a 1:1 ratio. A total of 200 women (100 per group) will be included in the study. A waitlist control strategy will be applied so that women in the control group will receive the PRIMI app after the follow-up measurement at 6 months. Outcomes will be assessed at baseline and at the 6-month follow-up. The PRIMI app, developed within the PRIMI project, is compatible with both Android and iOS. It contains weekly changing themes focusing on physical activity, diet, and health literacy throughout the 6-month intervention period. The app integrates behavior change techniques such as feedback and monitoring, goal setting, and instructions on how to perform the behavior. The app’s language can be switched among 4 common languages (Arabic, Somali, English, and Swedish), and all textual content can be accessed through audio files for listening. All procedures have been approved by the Swedish Ethical Review Authority (reference 2022-06733-01 and 2024-00135-02).

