### Study Design

The PRIMI trial is a 6-month 2-arm randomized controlled superiority trial (1:1 ratio) examining the effectiveness of an mHealth intervention (the PRIMI app) after childbirth on diet quality, and moderate-to-vigorous physical activity (primary outcome) as well as health literacy, BMI, self-efficacy, and self-rated health (secondary outcome) among first-generation migrant women compared with a waitlist control condition (Figure 3). Stakeholders, including migrant women and health professionals, were engaged during the development of the PRIMI app.

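### The claim of at least 80% power for 0.35 SD with 50 women per group is not supported by the stated inputs: it needs covariates to explain about 62% of outcome variance, and no such value is given

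*Protocol article*

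**What the plan says.** The sample-size paragraph of the protocol article (Statistical Analysis and Power Considerations) says: "A total of 100 women (50 per group) will provide at least 80% power (α=.05) to detect a minimally clinically relevant effect size". That effect is "a 0.35-SD difference in the primary and secondary outcomes". The basis is a set of simulated trials over varying sample sizes and parameter variances, with 100 runs per specification. The simulation inputs, any baseline-to-follow-up correlation and the sidedness of the test are not printed.

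The recruitment target of 200 (100 per group) is there to absorb dropout of up to 50%, so 50 completers per group is the number on which the power claim rests. The paragraph then adds that "we may consider recruiting fewer participants if the actual dropout rate is lower".

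The same section makes the primary analysis the group effect at 6 months adjusted for the baseline value. All models are also adjusted for age and time since childbirth, and educational attainment and birth region may be added. Outcomes are measured twice, at baseline and 6 months after randomization (Study Design).

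**The concern.** A 0.35-SD difference is modest, and 50 per group is small for it. An unadjusted comparison falls far short of 80%. Covariate adjustment can close the gap only if the covariates predict the 6-month value very well. The article states the power without any such condition and extends it to every outcome, including a single-item self-efficacy rating, a 0 to 100 health rating and short questionnaire measures of diet and activity. Baseline may fall anywhere in the first 6 months after birth, with follow-up 6 months after randomization, so close agreement between the two values cannot be assumed.

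Two things are at stake. If about 50 per group complete, the trial may well miss the effect it calls minimally clinically relevant, and a null result would say less about that effect than the stated power suggests. The figure also governs conduct, because it is the justification for recruiting fewer women when dropout is low.

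**Working it through.** **Inputs from the article.** n = 50 per group; difference d = 0.35 SD; α = 0.05; 1:1 allocation; one baseline and one follow-up value; baseline-adjusted analysis. Sidedness is not stated, so two-sided is taken as the default and one-sided is also tried. The correlation r is not stated, so every value of r below is an assumption.

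**1. Recruitment inflation.** 100 / (1 − 0.5) = 200. This reproduces.

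**2. Unadjusted power.** The noncentrality is d·√(n/2) = 0.35 × √25 = 1.75, against a two-sided critical value of 1.98 (t, 98 df). Power is 41.0% by noncentral t and 41.7% by normal approximation. One-sided 5% gives 53.7%. The stated 80% does not reproduce.

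**3. Baseline-adjusted power.** Adjustment shrinks the residual SD to √(1 − r²), so the noncentrality becomes 0.35 / √(1 − r²) × 5.

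| Assumed r | Noncentrality | Power, 50 per group | Difference detectable with 80% power (SD) | Completers per group for 80% at 0.35 SD |
|---|---|---|---|---|
| 0 | 1.75 | 41% | 0.57 | 130 |
| 0.5 | 2.02 | 52% | 0.49 | 98 |
| 0.6 | 2.19 | 58% | 0.45 | 83 |
| 0.7 | 2.45 | 68% | 0.40 | 67 |
| 0.8 | 2.92 | 82% | 0.34 | 48 |

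**4. What 80% requires.** Solving for 80% power at 50 per group gives r = 0.786, so r² = 0.62. The quantity that matters is the total variance explained by all covariates. If age, time since childbirth and any others are assumed to add 5% or 10% independently of baseline, the baseline correlation needed is √(0.618 − 0.05) = 0.75 or √(0.618 − 0.10) = 0.72. One-sided 5% with baseline alone still needs r = 0.72 (0.715).

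**5. Could simulation noise explain it?** With 100 runs the standard error near 80% is √(0.8 × 0.2 / 100) = 4 percentage points. If true power were 58%, the chance of 80 or more rejections in 100 is about 3 in a million; at 68% it is about 0.5%. Noise does not bridge the gap.

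**6. What the full 200 would give.** With 100 completers per group, power is 69% at r = 0 and 81% at r = 0.5; 80% needs r of about 0.48. With 80 per group (20% dropout) it is 72%, 79% and 87% at r = 0.5, 0.6 and 0.7.

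**The case against.** A reader might infer that the trial simply has 41% power and that the stated 80% is false. The article does not support that, for three reasons.

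- The figure came from simulation, the planned analysis adjusts for baseline, and the simulation inputs are not printed. A condensed article can leave such inputs to a fuller document. If they implied about 62% explained variance, the claim would follow. What can be shown is that the printed inputs do not support it.
- The 41% belongs to an unadjusted comparison, which is not the primary analysis. The adjusted values are the relevant ones, and they rest on assumed correlations. One exception applies: if 0.35 SD was meant in residual-SD units, adjustment adds nothing further and power is about 41%.
- Baseline is not the only covariate, so a correlation of 0.79 is not an absolute minimum.

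It is also fair to say that 50% dropout is an upper limit, that the reduction clause is discretionary, and that the article does not say how a null result would be read. The target of 200 is consistent throughout and is not itself an error.

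These points change the wording but do not remove the finding. The power statement carries no condition and covers all outcomes. BMI might reach the required correlation, but nothing in the article supports it for single-item self-efficacy or for the self-reported primary outcomes, which the Discussion says may be subject to recall and social desirability bias. The clause does permit drift towards 50 completers per group.

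**Conclusion.** The concern holds as a claim not supported by its stated inputs. At 50 completers per group and two-sided 5%, power for 0.35 SD is about 41% unadjusted and about 52% to 68% for assumed correlations of 0.5 to 0.7. Reaching 80% depends on about 62% of outcome variance being explained, or a correlation of about 0.72 to 0.79 depending on what the other covariates are assumed to add. A one-sided reading does not rescue it. The conclusion rests on the standard variance reduction from adjustment with one baseline and one follow-up value, and on 0.35 SD meaning the SD of the outcome. It would be answered, outcome by outcome, if the sponsor showed support for explained variance of that size.

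**What to change.** Restate the power at 50 completers per group as a function of an explicitly stated correlation or explained variance, and state the sidedness. For example: at two-sided 5%, 50 completers per group give 41%, 52%, 58% and 68% power for 0.35 SD at correlations of 0, 0.5, 0.6 and 0.7; the differences detectable with 80% power are 0.57, 0.49, 0.45 and 0.40 SD. Say which correlation is expected and why. Claim 80% only for outcomes where explained variance of about 62% can be supported.

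Remove the permission to recruit fewer than the planned 200 when dropout is lower. Those additional completers are what brings power to about 69% (r = 0) or 81% (r = 0.5) if all 100 per group are followed.

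The cost is a change of wording, a less favourable stated power and the loss of the option to stop recruitment early. No women beyond the planned 200 are needed. The change does not restore 80% power if dropout does reach 50%; it makes the stated figure match what the trial can then detect.

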### Ethical Considerations

We are not aware of any potential harms related to the PRIMI app. The intervention is designed to promote a healthy diet and physical activity in line with current guidelines and is based on our previous work [20,21]. Furthermore, as we hypothesize that the PRIMI app will have health benefits, it may pose an ethical dilemma not to provide the app to the control group as well. To address this, we will apply a waitlist control group strategy, and women in the control group will be offered the intervention after the trial has ended. This is considered an ethically reasonable choice of comparator. In summary, we believe that the PRIMI project is ethically motivated as there are potential health benefits and no known harms involved. Nevertheless, it is possible that the app may be perceived as stressful among some participants. Such information will be gathered through the process evaluation of user experience data.

Before giving informed consent, all participants will receive both oral and written information about the purpose of the study, its procedures, the voluntary nature of participation, and their right to withdraw from the study at any time without consequences or the need to provide a reason. All data will be anonymized before analysis and securely stored on encrypted servers for at least 10 years in accordance with Swedish legislation, accessible only to research team members involved in the analysis to protect privacy and confidentiality. No compensation will be provided for participation in the study. The PRIMI trial has received ethics approval from the Swedish Ethical Review Authority (reference 2022-06733-01 and 2024-00135-02) and is being conducted in accordance with the Declaration of Helsinki. Any deviations from what is described in this study protocol will be reported on ClinicalTrials.gov and in the manuscript reporting the results of the trial.

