^a^The behavior change techniques applied were based on the Behavior Change Technique Taxonomy version 1 [32]: information about health, social, environmental, and emotional consequences of behaviors; feedback and monitoring; identification of the self as a role model; verbal persuasion about capability; focus on past success; pros and cons; goal setting (behavior); action planning; discrepancy between current behavior and goal; behavior substitution; habit formation; prompts and cues; and instructions on how to perform the behavior.

The app also has features such as goal setting, registration with feedback for diet and physical activity, prompts for positive self-talk (eg, encourage users to recognize their efforts), healthy food recipes, supermarket tours, and video-recorded workout programs. Goals refer to the number of workout programs that users want to complete in a week (ie, 1-5), and they can be easily changed by users. The registration with feedback feature includes a prompt to complete a 6-item weekly questionnaire that addresses dietary and physical activity behaviors. When completed, users access feedback that summarizes their responses in terms of diet score and total activity minutes, graphically illustrated with bars and text using a “traffic light” approach (green=reached the recommendation, yellow=almost reached the recommendation, and red=far from reaching the recommendation) as provided by the National Board of Health and Welfare in Sweden [30]. Thus, a green light for physical activity indicates that users have reported at least 150 minutes of moderate-to-vigorous physical activity for that week, whereas a green light for the diet score represents at least 75% of the maximum score based on users’ weekly consumption of fruit and vegetables, fish and seafood, and sweets and sugary drinks.

The PRIMI app additionally contains healthy recipes developed by the Swedish Food Agency (Keyhole-labeled recipes) [33], as well as international healthy dishes developed by the registered dietitians in the PRIMI group. In addition, videos aiming to facilitate health awareness during grocery shopping are provided on the app. The physical activity module contains video-recorded workout programs at 3 levels (basic, intermediate, and advanced) with a Tabata-style interval format.

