All content is free and available for all users, who can choose to engage with the app as preferred. Intended use will be defined as at least one engagement session per week where users complete the weekly registration, receive feedback on their health behaviors, and access the weekly theme. Users who accept push notifications will receive reminders 2 to 3 times per week depending on their preferences.

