### Eligibility and Recruitment

Eligible women will be recruited through health care (eg, maternal and child health care) throughout Sweden. Inclusion criteria are first-generation migrant women who have given birth ≤6 months before, aged ≥18 years, and who would prefer to receive health-related information in any of the provided languages (ie, Arabic, Somali, English, and Swedish). No exclusion criteria will be applied.

Health care professionals will briefly inform eligible women about the trial. Women who express interest will receive additional information, including contact details for the research team. Informed consent will be obtained by health care professionals during subsequent visits or via the women returning signed consent forms. Inclusion criteria will be formally assessed based on information provided in the baseline questionnaire, which will be delivered digitally to participants via their mobile phones after they have given informed consent.

Recruitment will begin in September 2025, at 3 sites across the regions of Sweden, with each site involving 5 to 10 units. Health professionals (eg, nurses) at each unit will be introduced to the study and its procedures through in-person visits by research team members, who will provide ongoing support throughout the recruitment period. We will continue recruitment until the required number of participants has been reached. However, if recruitment is slow, we will consider additional sites and avenues other than health care channels, such as nongovernmental organizations, associations, and social media.

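### The article seeks unwanted effects only through app-arm experience questions, so the trial will have no between-arm estimate of injury, new symptoms or stress about diet and activity

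*Protocol article*

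**What the plan says.** Ethical Considerations opens with "We are not aware of any potential harms related to the PRIMI app" and sums up that "there are potential health benefits and no known harms involved". It then allows that some participants may experience the app as stressful, and adds: "Such information will be gathered through the process evaluation of user experience data".

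The Process Evaluation section defines that source: "User experience data will be collected at the 6-month follow-up by asking intervention group participants about their experiences of the PRIMI app". Interviews with a subsample of women about how the intervention was perceived are added.

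On who enters, Eligibility and Recruitment says "Inclusion criteria are first-generation migrant women who have given birth ≤6 months before, aged ≥18 years", sets no minimum interval since birth, and states "No exclusion criteria will be applied". On what is offered, Content and Features lists "video-recorded workout programs at 3 levels (basic, intermediate, and advanced) with a Tabata-style interval format" and says "All content is free and available for all users, who can choose to engage with the app as preferred".

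Both arms are assessed at baseline and 6 months. The secondary outcomes include the EQ-5D visual analogue scale (0 to 100) and BMI from self-reported weight and height.

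**The concern.** Complaints such as pain, injury or stress can arise in the months after a birth whether or not a woman has the app. Reports from the app arm alone therefore neither implicate the app nor clear it. Randomization supplies a control group that would settle the matter as far as the numbers allow, and both groups already receive a 6-month questionnaire. As described, that control group is not used for this purpose.

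The Conclusions section envisages national use if the app proves effective. The trial would bring to that decision a randomized estimate of benefit, but no comparative estimate of injury, new symptoms or stress about diet or activity. With broad entry and an exercise component, these are the effects a reader would ask about.

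**Working it through.** The plan states no figure on this point, so there is none to reproduce. The check has two parts.

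**1. What is collected, by arm**

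| Possible effect | App arm | Control arm | Between-arm estimate |
|---|---|---|---|
| App felt to be stressful | Experience questions at 6 months, subsample interviews | Not applicable | None, and none is meaningful |
| Stress about diet or activity in general | Only if it surfaces in the above | None described | None |
| Injury, new or worsened symptoms | None described | None described | None |
| General health | EQ-5D visual analogue scale | Same | Yes, coarse |
| BMI | Self-report | Same | Yes, but says nothing on injury or stress |

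**2. What the numbers could support**

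Responders per arm: the power section plans 100 randomized per group and allows dropout of up to 50%, so 100 × (1 − 0.5) = 50 at worst and 100 at best.

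- *Zero reports in the app arm.* The one-sided 95% upper limit is 1 − 0.05^(1/n). For n = 50 it is 5.8%; for n = 100 it is 3.0%.
- *Reports expected with no app effect.* The documents give no background rate. Assuming 10-20%: 0.10 × 50 = 5 up to 0.20 × 100 = 20 reports in the app arm.
- *What the visual analogue scale can show.* The unadjusted 95% half-width for a difference in means is 1.96 × √(2/n) SD: 0.39 SD for n = 50 and 0.28 SD for n = 100. Baseline adjustment would narrow this. If, as an assumption, 5% of app users were 1 SD worse because of an injury, the mean would shift by 0.05 × 1 = 0.05 SD, well inside either interval.
- *What two-arm items would give.* The 95% half-width of a risk difference, with the same rate p in both arms, is 1.96 × √(2p(1 − p)/n). The rates are assumptions.

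| p | n = 50 per arm | n = 100 per arm |
|---|---|---|
| 10% | ±11.8 points | ±8.3 points |
| 20% | ±15.7 points | ±11.1 points |

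- *Power of such a comparison* (two-sided 5%, assumed rates):

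| Rates | 50 per arm | 100 per arm |
|---|---|---|
| 5% v 10% | 16% | 27% |
| 5% v 15% | 38% | 66% |
| 10% v 25% | 51% | 80% |

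The two-arm comparison is imprecise, but it yields an interval. One-arm data yield no between-arm estimate at any sample size.

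**The case against.** The strongest reply is that the stated route suits the effect it is meant for. The sentence in Ethical Considerations concerns only whether the app is felt to be stressful, and only women who have the app can say so. That stands: asking app users is reasonable and should continue.

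A second reply is that, for physical effects, the article is merely silent, and a condensed article may leave adverse-event questions to a fuller document. That stands in part. If the full protocol already puts such items to both arms, this point falls away for physical effects. What keeps it from being only a note on missing detail is that the article does say how unwanted effects will be gathered, and that choice leaves the control arm out.

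A third reply is that both-arm items would have low power, and that unblinded women may recall activity-related complaints differently by arm. Both are true. They argue for descriptive reporting, but not for leaving the items out.

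A reader might also infer that the article contradicts itself by declaring no known harms while combining open entry with interval workouts. It does not. The phrase describes present knowledge, the trial lists no safety objective, and the two positions can coexist. Nor are the workouts prescribed: they are optional, include a basic level, and users choose their own weekly goal. The app's advice is described as guideline-based and covers bodily changes after childbirth, and both arms keep standard care.

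**Conclusion.** The point holds as a cheap improvement to the safety information, not as an error in a stated analysis. Followed as written, the trial would give no between-arm estimate of injury, new or worsened symptoms, or stress about diet or activity. App-arm silence would leave rates up to roughly 3-6% unexcluded, and app-arm reports could not be separated from background.

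It would be too strong to conclude that the trial can learn nothing comparative about harm. The EQ-5D visual analogue scale is collected in both arms and could reveal a net worsening of general health; its limit is that it cannot say what happened or to how few. The primary and secondary effectiveness analyses are unaffected.

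The zero-event limits rest on 50 to 100 responders per arm, which follows from the plan's own dropout allowance. The background rates of 10-20% and the event rates in the power figures are assumptions. The conclusion that one-arm data give no comparison does not depend on them.

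**What to change.** Add two or three identical closed items to the 6-month questionnaire in both arms:

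- injury, or a new or worsened symptom, during physical activity;
- health care contact because of it;
- stress about diet or activity.

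Report counts and risk differences with confidence intervals by randomized arm. Label them descriptive, because precision is low and participants know their allocation. Keep the app-specific experience questions and interviews for the intervention arm as planned.

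The cost is translation of the items into four languages, about one minute of respondent burden, one descriptive table and probably an ethics notification. No change to eligibility, exercise content or care is proposed.
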